#### CBT treatment group

Individual CBT sessions (sessions 5 to 8 in the control group) are conducted by a CBT-trained investigator and focus on reviewing and adapting the strategies discussed in the group sessions. The sessions last between 30 and 90 min and are designed to develop a list of strategies adapted to the patient's daily life, addressing various environments such as the supermarket, parties, home and exposure to advertising. The patient's desire to drink is regularly assessed using a visual analog scale (VAS).

#### VR-CET treatment group

For the VR-CET group, individual exposure sessions (sessions 5 to 8) are conducted by an investigator trained in CBT. Prior to the exposure sessions, each patient will establish a hierarchy of four virtual environments: exposure to alcohol advertising, home, supermarket, and parties (cf. Figure 2) ranging from the simplest to the hardest. The duration of exposure to each virtual environment varies according to the time needed to reduce the participants’ craving. Participants move on to the next environment when a comfortable level of emotion or craving is reached, and exposure can be repeated if necessary. If craving remains high at the end of a session, it is extended. After exposure, patients benefit from a 5 to 10 min VR relaxation session. Craving is regularly assessed using a VAS before, during and at the end of each session.

**Fig. 2 Fig2:**
[figure not shown]
Screenshots of the virtual environments utilized in the present study

### Apparatus

For the VR-CET group, the virtual reality device is as follows:An HP reverb G2 virtual reality headset with 2160 × 2160 resolution per eye and position sensor integrated into the headset.Two motion controllers in the form of joysticks in each hand that locate the position of the thumb, index and middle fingers in contact with the buttons. In addition to walking, the wireless joysticks enable subjects to interact with 3D objects (taking a drink, picking up a bottle, etc.). The subject thus produces equivalent movements in real time and explores synthetic situations visually.Victus laptop by HP Laptot 16-s0025nf NVIDIA GeForce RTX 4060.

The software exploited to run the virtual reality environments was C2Care. In the alcohol addiction care offering, we have selected 4 environments, following a focus group in 2019, offering distinct scenarios inducing the desire to drink. The environments selected are as follows (Cf. Figure 2):Heading for the metro, where there is a large alcohol advertisement;Go to the supermarket and pass through the alcohol aisle;Find yourself alone at home with a bottle of alcohol on the table;Going to a party.

### Criteria for discontinuing or modifying allocated interventions

Participants can end their participation in the research at any time, and the investigator may do so for safety reasons or in the best interest of the participant. Temporary break in participation may occur in cases of persistent psychological distress, trauma during sessions, or discomfort related to virtual reality. Early termination may occur if inclusion criteria are not met. Pregnancy, protective measures, or enrollment in another study will result in definitive dropout. Absence from group sessions (50%) may lead to exclusion.

### Evaluation outcomes

#### Primary outcome

The primary outcome is the cumulative number of standard drinks consumed (in grams of pure alcohol) at 8 months, as reported by patients. As a reminder, in France, 1 standard drink = 10 g of pure alcohol = 1 unit of alcohol [25]. Alcohol consumption is estimated retrospectively by patients every month using the Timeline Follow-Back (TLFB) method, a widely used method that has demonstrated good psychometric properties and superiority over free recall [26]. This method allows retrospective estimation of alcohol consumption over a specified period of up to one year. Estimates of alcohol consumption (in standard drinks) are collected monthly by the research team, either in person or by telephone, to reduce recall bias and improve the performance of this method over time [27].

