
## Methods/Design

### Study setting and population

Study data will be collected in day hospitals (DH) within the addiction departments of public hospitals. For this research, four centers in the Paris area will be involved in recruiting patients. The four recruiting centers are: 1) Department of Addictions—Hôpital Albert Chenevier—CHU Henri Mondor—APHP – Créteil, 2) Department of Addictions—Hôpital Fernand Widal—Nord—Université de Paris—APHP – Paris, 3) Department of Addictions—Centre hospitalier des Quatre Villes – Sèvres, 4) Department of Addictions—Tolbiac Day Clinic – Paris. Recruitment will be done by the investigating physician at the time of admission to the DH during an individual consultation. If the patient is eligible for the study, the full protocol will be presented and reviewed during an individual consultation at the DH enrollment visit.

The following inclusion criteria apply: i) 18 to 80 years of age at the time of enrolment; ii) patients with a diagnosis of AUD according to DSM-5 criteria (American Psychiatric Association, 2013); iii) patients who had been abstinent for at least 15 days; iv) patients who can speak, understand and read French; v) patients who have signed an informed consent form and who are affiliated to a health insurance plan.

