### Sample size

To determine the number of participants needed for the study, we randomly selected 15 patients with alcohol-related disorders (AUD) who were already being treated at the Albert Chenevier Day Hospital's addiction department. Their cumulative alcohol consumption was monitored at two, five and eight months after admission to estimate the average daily consumption over eight months. The target consumption was calculated on the basis of the recommendations of the European Medicines Agency [39], aiming at a reduction of at least two risk levels according to the World Health Organization. To achieve a statistical power of 0.8, considering a risk α of 0.05 with a two-sided hypothesis, 65 patients per group are required. Assuming a drop-out rate of 20%, 78 patients per group need to be recruited, for a total of 156 patients for both groups. See Table 2 for recruitment procedure.

**Table 2 Tab2:** Recruitment procedures

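### The adjusted model of cumulative drinks at 8 months contains no measure of drinking before treatment, although AUDIT-C is already collected at enrolment

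*Protocol article*

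**What the plan says.** All references are to the protocol article.

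- **Outcome** (Primary outcome): "The primary outcome is the cumulative number of standard drinks consumed (in grams of pure alcohol) at 8 months, as reported by patients". On collection: "Alcohol consumption is estimated retrospectively by patients every month using the Timeline Follow-Back (TLFB) method". On the reach of the instrument: "This method allows retrospective estimation of alcohol consumption over a specified period of up to one year".
- **Entry** (Study setting and population): eligible patients include "patients who had been abstinent for at least 15 days".
- **Analysis** (Statistical methods): the 8-month total is compared between arms by an independent-samples t-test. Complementary generalized linear models adjust for the minimization factors and the number of sessions.
- **Minimization factors** (Treatment groups): center, medication supporting abstinence, treatment for AUD in the past five years, consumption goal, and DSM-5 severity. Randomization takes place at M1, after the four group sessions.
- **Drinking at enrolment** (Secondary outcomes): AUDIT-C, described as three questions on alcohol consumption, is taken at enrolment, M2, M5 and M8.
- **Sizing** (Sample size): the target consumption was set "aiming at a reduction of at least two risk levels according to the World Health Organization".

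**The concern.** How much a patient drank before treatment is a natural candidate predictor of how much that patient drinks over the next 8 months. The article names the covariates of its adjusted model, and prior drinking is not among them. DSM-5 severity and treatment history are related to it, but neither is an amount of drinking. One measure, AUDIT-C, is already taken at enrolment and so precedes randomization, which makes it a legitimate baseline covariate at no extra cost.

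The entry criterion adds a second difficulty. Patients are already abstinent, so drinking just before inclusion is zero by eligibility and cannot describe their usual intake. A starting level in g/day needs a recall window that ends when the current abstinence began, and the text describes none.

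At stake are the precision of the adjusted estimate, protection of that estimate against chance imbalance in prior drinking, and the ability to describe how heavily the trial population drank before treatment. The validity of the primary test is not at stake.

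**Working it through.** **1. The plan's own figure.** The article states: "To achieve a statistical power of 0.8, considering a risk α of 0.05 with a two-sided hypothesis, 65 patients per group are required". It gives neither a mean difference nor an SD, so 65 cannot be reproduced forwards. Solved backwards with the normal approximation, d = (1.960 + 0.842) × √(2/65) = 0.491; the t-based solution is 0.495. No covariate enters this calculation, so the sample size does not depend on a baseline measure.

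**2. Does the outcome or the sizing target need a starting level?** The only reference intake described is that of 15 pilot patients: "Their cumulative alcohol consumption was monitored at two, five and eight months after admission to estimate the average daily consumption over eight months". That is intake after admission. The primary outcome can be put on the same scale without a baseline. At 10 g per drink and 8 × 30.4375 = 243.5 days:

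- 20 g/day: 20 × 243.5 / 10 = 487 drinks
- 40 g/day: 40 × 243.5 / 10 = 974 drinks
- 60 g/day: 60 × 243.5 / 10 = 1,461 drinks

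Neither the t-test nor this conversion uses a patient's earlier level.

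**3. What the adjusted model holds.**

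| Term | Amount of prior drinking? |
|---|---|
| Center (4) | No |
| Medication supporting abstinence (2) | No |
| Treatment history, five years (2) | No |
| Consumption goal (2) | No |
| DSM-5 severity (3) | No, but related |
| Number of sessions | No |

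The minimization factors use 3 + 1 + 1 + 1 + 2 = 8 parameters. A linear AUDIT-C term adds one.

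**4. Would a look-back from inclusion supply the missing value?** Let W be the window in days and A the days abstinent at entry, with A ≥ 15. The share of days that are zero by abstinence is min(A, W)/W.

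- W = 15: 15/15 = 100% for everyone
- W = 30, A = 15: 15/30 = 50%
- W = 30, A = 20: 20/30 = 67%
- W = 30, A ≥ 30: 100%

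A window of a month or less is therefore at least half zeros, and all zeros for anyone abstinent throughout it. A usable window has to sit before the abstinence, which the stated one-year reach of the TLFB permits.

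**5. Size of the gain.** In a linear model, adding a covariate multiplies the residual variance by 1 − r², where r is its partial correlation with the outcome given the terms already in the model. The documents give no value for r, so no figure can be derived.

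**The case against.** The strongest reply is that this is a condensed article. The assessment schedule (Table 1) is not shown, the contents of the inclusion questionnaire are not listed, and the time of the first TLFB is not stated. The full protocol may already record pre-abstinence intake, and an analysis plan may add covariates. This stands as a limit on what can be said about collection. It carries less weight for the model, because the article states the adjustment set and prior drinking is not in it.

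It can also be said that severity and treatment history already carry part of the information. That stands too: any gain is incremental to them.

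Four stronger readings are tempting, and the documents do not support them.

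- *That no starting level exists.* AUDIT-C is taken at enrolment, and an unseen table cannot show that a TLFB is absent.
- *That the two-level fall in WHO risk cannot be reported as planned.* No endpoint or responder rate is defined on that fall. It appears only as a planning target, and the only intake described beside it is the pilot patients' intake after admission.
- *That drinking can only rise from an enforced zero, so no reduction can be shown.* The comparison is between arms, and one arm can drink less than the other over 8 months whatever the entry value.
- *That the loss is equivalent to a definite number of patients.* Assumed correlations of 0.3 and 0.5 would give 130/(1 − 0.09) = 143 and 130/(1 − 0.25) = 173 in place of 130. Those correlations are not in the documents, the sum ignores the factors already in the model, and it does not apply to the unadjusted t-test.

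**Conclusion.** The point holds as a modest, correctable weakness in the complementary adjusted analysis. The stated covariates omit prior drinking while a measure of it is already collected before randomization. The primary between-arm comparison is valid as it stands, and the sample size is unaffected.

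The size of the gain cannot be derived from the documents. It depends on how strongly enrolment AUDIT-C predicts the 8-month total once center, medication, treatment history, goal and severity are accounted for.

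Two assumptions remain. First, the AUDIT-C questions asked at enrolment must reach back beyond the abstinent period; the article does not give their recall period. Second, Table 1 and the full protocol must not already provide a pre-abstinence TLFB. If they do, what remains is to state its window.

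**What to change.** 1. **Model.** Prespecify the enrolment AUDIT-C score as a covariate in the adjusted model of cumulative drinks at 8 months, alongside the stated terms. Use it for every patient, so that all are on one common scale; do not mix TLFB values for later patients with AUDIT-C for earlier ones. State the recall period of the questions. Leave the t-test unchanged. The cost is one sentence in the analysis plan and one model parameter, with no new data collection. As the trial is open-label, record the change before any outcome is compared by arm.

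2. **Description, if not already recorded.** At inclusion, take one TLFB over a fixed window that ends on the day before the current abstinence began, and report starting intake in g/day. The cost is a short interview and an amendment. Recruitment began in October 2023, so patients already enrolled would have no value. This measure therefore serves to describe newly enrolled patients and should not replace AUDIT-C in the model.

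A new outcome based on WHO risk levels is not needed to resolve this point.

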#### Secondary outcomes

Craving is assessed by the Transaddiction Craving Triggers Questionnaire (TCTQ) [28]. This is an instrument designed to assess what triggers craving. The questionnaire is completed at inclusion, M2, M5, and M8. Craving is also assessed using a VAS (0 to 10) at each exposure session [29] and on a monthly basis after M2, in the same way as for the primary outcome.

The frequency of hazardous drinking episodes is assessed with the AUDIT-C (Alcohol Use Disorders Identification Test) questionnaire [30], an abbreviated version of the AUDIT self-report questionnaire [31] that includes three questions about the patient's alcohol consumption. These data are collected at enrollment and at treatment phases M2, M5, and M8. Finally, reported alcohol consumption is correlated with weekly DH toxicology monitoring, if this is routinely performed at the recruiting centers. Weekly toxicology screenings for ethyl glucuronide (EtG), if performed as part of the routine care at the recruiting centers, will be recorded in the logbook.

Anxiety is assessed by the Generalized Anxiety Disorder-7 (GAD-7) questionnaire [32]. This instrument is designed to screen for generalized anxiety disorder and may also help to identify panic disorder, social anxiety disorder, and posttraumatic stress disorder. It is administered at inclusion, M2, M5, and M8.

Depression is assessed by the Patient Health Questionnaire-9 (PHQ-9) [33]. This instrument collects information on the presence and intensity of depressive symptoms. Data is collected at inclusion, M2, M5, and M8.

Self-efficacy is assessed by the Sense of Self-Efficacy Questionnaire, originally developed in German by Matthias Jerusalem and Ralf Schwarzer [34]. It is administered at inclusion, M2, M5, and M8.

Rumination is assessed by the 15-item Perseverative Thinking Questionnaire (PTQ). This is a widely used self-report measure of repetitive negative thinking [35]. It is administered at inclusion, M2, M5, and M8.

The state of presence in virtual reality is measured by the QEP questionnaire (Questionnaire sur l'État de Présence) developed by the UQO Cyberpsychology Laboratory (2002) [36, 37]. This survey is conducted at M2 for the participants randomly assigned to the VR-CET group.

Cybersickness risk is assessed after each VR-CET session using the Cybermalaise Questionnaire from the UQO Cyberpsychology Laboratory [38].

All questionnaires are completed by DH patients at inclusion and M2. The scheduled assessments from M3 to M8 are conducted by telephone (Cf. Table 1).

**Table 1. Tab1:**
[figure not shown]
Schedule of enrolment, interventions, and assessments

### Sample size

To determine the number of participants needed for the study, we randomly selected 15 patients with alcohol-related disorders (AUD) who were already being treated at the Albert Chenevier Day Hospital's addiction department. Their cumulative alcohol consumption was monitored at two, five and eight months after admission to estimate the average daily consumption over eight months. The target consumption was calculated on the basis of the recommendations of the European Medicines Agency [39], aiming at a reduction of at least two risk levels according to the World Health Organization. To achieve a statistical power of 0.8, considering a risk α of 0.05 with a two-sided hypothesis, 65 patients per group are required. Assuming a drop-out rate of 20%, 78 patients per group need to be recruited, for a total of 156 patients for both groups. See Table 2 for recruitment procedure.

**Table 2 Tab2:** Recruitment procedures

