	**Number of subjects**
Total number of subjects selected	156
Number of centers	4
Inclusion period (months)	24

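### The 20% drop-out allowance multiplies 65 by 1.20 instead of dividing by 0.80, so 156 patients leave about 62 per group rather than the 65 required

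*Protocol article*

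**What the plan says.** The calculation is in the Sample size section of the protocol article. The design values are given by "To achieve a statistical power of 0.8" and "considering a risk α of 0.05 with a two-sided hypothesis", and the result before any allowance for losses is "65 patients per group are required". The allowance follows in one sentence: "Assuming a drop-out rate of 20%, 78 patients per group need to be recruited, for a total of 156 patients for both groups".

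Table 2 repeats 156 beside the label "Total number of subjects selected". The abstract, the end of the Introduction and the Discussion also carry it, and the Discussion presents the sample size as an improvement on previous research.

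Three other statements bear on the point:

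- The Statistical methods section compares the primary outcome, cumulative standard drinks at 8 months, between groups with Student's t-test.
- The section on missing data says that patients who leave will not be replaced, and that missing data will be handled by multiple imputation.
- The section on analysis populations makes intention-to-treat the main analysis of the primary endpoint.

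**The concern.** The paragraph gives three figures that should fit together: 65 required per group, 20% drop-out and 78 recruited per group. Removing 20% of 78 should leave at least 65, and it does not. The figure of 78 results from adding 20% of the required number to itself. That treats the 13 extra patients as 20% of 65, whereas a drop-out rate applies to those recruited, and 13 is only 16.7% of 78.

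What is at stake is whether the stated justification is true. As printed, 156 patients, 20% drop-out and 80% power cannot all hold. The figure will presumably be carried into the results paper, and since leavers are not replaced, nothing in the conduct of the trial makes up the difference. The three figures are all printed and disagree, so this is not a detail that a condensed article has left out.

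**Working it through.** **Inputs, all from the Sample size section:** two-sided α = 0.05; power 0.80; n = 65 per group before losses; drop-out rate 0.20; 78 recruited per group, 156 in total. Equal allocation is implied by the equal group sizes. The difference to be detected and its standard deviation are not given as numbers, so the 65 itself cannot be checked and is taken as stated.

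**1. Reproducing the plan's figure.**
65 × (1 + 0.20) = 78 per group, and 2 × 78 = 156. This matches exactly.

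**2. The standard allowance.**
n / (1 − drop-out) = 65 / 0.80 = 81.25, rounded up to 82 per group, or 164 in total. That is 8 more than 156. Check: 82 × 0.80 = 65.6, which meets 65. Rounding cannot account for a gap of 4 per group.

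**3. What 78 per group delivers.**
- At 20% drop-out: 78 × 0.80 = 62.4 per group, which is 2.6 below 65.
- Over both groups: 156 × 0.80 = 124.8, against 130 required.
- Largest drop-out that still leaves 65: 1 − 65/78 = 13/78 = 16.7%.

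**4. Effect on power.** The standardised difference d has to be back-solved as the value at which 65 per group gives exactly 80% power.
- Normal approximation: d = (1.960 + 0.842) × √(2/65) = 0.491.
- Noncentral t, matching the planned t-test: d = 0.495.

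Holding d fixed and lowering the number per group:

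| Evaluable per group | Power, normal approximation (d = 0.491) | Power, noncentral t (d = 0.495) |
|---|---|---|
| 65 | 80.0% | 80.0% |
| 62.4 | 78.4% | 78.4% |
| 62 | 78.1% | 78.1% |

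The loss is 1.6 to 1.9 percentage points.

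**5. Sensitivity to the back-solving.** The 65 may itself have been rounded up from a value just above 64. In that case d is about 0.495 on the normal approximation, and power is 79.0% at 62.4 and 78.7% at 62 per group. Over these assumptions the power at 20% drop-out lies between about 78% and 79%.

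**The case against.** The arithmetic cannot be defended, but its importance can be disputed, and most of that case stands.

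*The effect is small.* The shortfall is 8 recruits in total and roughly 2 points of power. No estimand, test or analysis population changes, and 156 is enough if drop-out stays at or below 16.7%. This stands and limits the point to a minor correction. A reader might infer that the trial is seriously underpowered. The article's figures do not show that.

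*Drop-outs are not worthless.* The main analysis is by intention to treat with multiple imputation, and consumption is collected monthly, so a patient lost late still contributes earlier months. About 62 per group is therefore nearer a floor than an expected effective size. This also stands as a comment on size. It does not rescue the figure of 78, because an allowance for drop-out treats leavers as lost and the paragraph claims no gain from imputation.

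*The effect size is not the sponsor's.* The value 0.495 is derived from the 65 and is not stated in the article. It serves to gauge the loss and should not be published as the design effect.

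*Two further inferences go beyond the text.* Randomisation takes place at M1, after the group sessions, and the discontinuation criteria say "Absence from group sessions (50%) may lead to exclusion". A reader might infer that 156 counts patients at enrolment, so that first-month losses reduce the groups further. The article does not settle this. The words used for recruitment and selection point towards enrolment, but a number per group points towards a randomised count, since groups exist only after randomisation. Nor does it say when the 20% begins, so adding a separate early loss could count the same patients twice. The exclusion is discretionary and has no stated rate. A condensed article may also leave these definitions to the full protocol.

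A reader might also expect the adjusted models to recover the lost power. The Statistical methods section makes them complementary to an unadjusted t-test, and nothing is given from which the gain could be estimated.

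**Conclusion.** The point holds as an arithmetic error in the Sample size section. Allowing for 20% drop-out from 65 per group takes 82 per group and 164 in total, not 78 and 156. At the stated drop-out rate, 156 patients leave 62.4 per group; they leave 65 only up to 16.7%.

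The head-count statements rest on the article's figures alone. The statement that power is about 78% instead of 80% rests on three assumptions: the 65 is correct, drop-outs contribute no information, and d is the back-solved 0.495. If imputation recovers information from partial follow-up, the real loss is smaller.

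The severity is a minor correction: a definite and checkable error in a headline figure, with a small effect on the trial. The conclusion does not depend on whether 156 is counted at enrolment or at randomisation.

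**What to change.** Correct the Sample size paragraph in one of two ways, and carry the same qualification to Table 2:

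1. Keep 156 and state that it provides 65 per group for drop-out of up to 16.7%; or
2. Keep 20% drop-out, state that 156 leaves about 62 per group, and restate the power. It is about 78% here, but the sponsor should recalculate it from its own difference and standard deviation. Note that 164 would be needed for 80%.

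Neither option needs extra patients or changes the analysis or any trial procedure. The cost is one corrected sentence, a note to the table and a slightly less favourable stated figure.
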